#### Emotion focused skills training

2.5.2

We offer parent training based on the Emotion focused skills training for parents (EFST-P). The EFST-P is a manualized group program for parents (Dolhanty et al., 2022). It uses an emotion-processing, skill-based approach that provides parents with simple, practical tools that they can use immediately in their families. The EFST-P can be delivered in different ways (full-day workshop or weekly group meetings; Dolhanty et al., 2022). In the present study, 6 weekly group sessions of 100 min each are conducted by two psychologists. The aim of the program is to overcome feelings of shame, guilt or fear that interfere with effective parenting. Parents learn to navigate their emotions by understanding children’s emotions and needs. The EFST-P focuses on developing the following four key skills:

(1) Validating children’s feelings: Instead of trying to solve the child’s problems quickly, parents are taught to recognize the child’s feelings and put them into words. This should help the child process their feelings and calm down.(2) Increasing motivation: Parents learn why they find it difficult to understand and validate their child’s feelings. So-called emotional traps are introduced, which can prevent parents from being emotionally present with the child.(3) Apologizing: By apologizing to the child for their own misbehavior, parents learn to take responsibility for their relationship with the child and transform it. The parents discuss how their behavior must have affected the child and what they would like to change in the future.(4) Setting appropriate boundaries for children: Parents learn to set clear but flexible boundaries without judging the child.

Imaginative two-chair work is used to help parents understand emotional traps in dealing with their child and to facilitate emotionally focused processing of the child’s behavior (Dolhanty et al., 2022). This, in turn, is intended to strengthen parents’ self-efficacy and mentalization skills (understanding behavior in terms of mental states).

#### Treatment fidelity

2.5.3

To ensure fidelity to the material as well as adequate engagement with the content of the intervention, the students, who carry out the intervention, receive training from a staff member of our institute. Furthermore, we created a manual explaining every step of the intervention in detail. During training, these guidelines and materials are discussed in a small group of approximately 10 students at a time. All activities used in the intervention are then demonstrated within the group of students. This is done to ensure that the students are equipped to carry out the intervention program. Each school visit is led by an experienced student. The students also meet shortly before the visit to discuss the implementation in advance.

### Outcome measurements

2.6

The demographic variables recorded for parents, students and teachers are age, gender, migrant background and German language skills. Teachers are also asked how many years they have been teaching. College students are asked about their subject, semester of study and any previous medical experience, and medical field of interest. Parents are also asked about their socioeconomic status (income, highest level of education). Children are asked about their age, gender and grade. Sociodemographic data is collected through self-report in the first survey. The first survey for the teachers is at t_3_.

To assess mental health literacy children are presented with one of three case vignettes, with a different case vignette presented at each time point of the survey. The order in which each vignette is presented to each child is counterbalanced by intraindividual block randomization to avoid possible sequence effects. The three case vignettes used are self-designed cases based on the vignettes used to measure mental health literacy by Jorm et al. (1997). The case vignettes are similar to Jorm’s vignettes in that the case is a description of a situation in which mental distress or illness can be identified. However, in contrast to Jorm’s case vignettes, the case vignettes used here portray three children (Noah, Kim, Conny) rather than adults as affected. The three names were chosen to be gender neutral. In Noah’s case, symptoms of depression are described; in Kim’s case, symptoms of attention deficit hyperactivity disorder are described; and in Conny’s case, symptoms of conduct disorder are described. For each case vignette, there are two open questions and 14 closed questions. The open questions are, “What do you think is Noah’s [Kim’s/Conny’s] problem?” and “What do you think would be the best way to help Noah [Kim/Conny]?” The closed questions relate to the assessment of the severity and origin of the stress, as well as the assessment of self-help strategies in the situation described: E.g., “Do you think Noah [Kim/Conny] might have a mental health problem?” or “What do you think could improve Noah’s [Kim’s/Conny’s] situation - If Noah [Kim/Conny] stayed at home? Children respond using a simplified 3-point Likert scale (1 = Yes, 2 = Maybe, 3 = No), adapted to their cognitive and developmental level. The case vignettes were first tested for comprehension in a fourth grade-class, in which n = 22 children commented on the comprehensibility and were subsequently revised. Question wording and selection were based on theoretical considerations of the knowledge component of mental health literacy, items from a validated adult mental health literacy questionnaire (MHLq-SVa; Campos et al., 2022), and consultation with experts in the field to ensure item content validity.

An adapted German version (Sharples et al., 2017; Kaess et al., 2019) of the General Help-Seeking Questionnaire (GHSQ; Wilson et al., 2005) is administered to assess the intentional help-seeking behaviors of children and parents concerning mental health issues. Parents respond on a 7-point Likert scale ranging from 1 (extremely unlikely) to 7 (extremely likely). Children respond using a simplified 3-point Likert scale (1 = agree, 2 = neutral, 3 = strongly disagree). An example item reads, “If you [or your child] were experiencing a mental health problem (e.g., feeling stressed, angry, depressed, anxious, or worried), how likely is it that you would seek help from the following people?” The questionnaire lists 8 potential sources of help, including both informal (e.g., friends, family members) and formal (e.g., doctor, psychologist) options, as well as, “I would not seek help from anyone” and an open-ended response to specify other people not listed. For scoring purposes, the sum of the listed eight help sources is used to calculate an overall score for intentional help-seeking behavior. Higher scores indicate greater help-seeking intentions. The instrument demonstrates good to very good internal consistency (Cronbach’s *α* = 0.85) and strong test–retest reliability over a three-week period (*r* = 0.92; Wilson et al., 2005).

To assess actual help-seeking behavior, an adapted German version (Sharples et al., 2017; Kaess et al., 2019) of the Actual Help-Seeking Questionnaire (AHSQ; Rickwood and Braithwaite, 1994) is used. Children and parents are asked to tick all formal and informal sources, from a provided list of 8 potential sources (see the GHSQ), from which they have sought help in the past 6 months because they/their child experienced a mental health problem (were stressed, angry, depressed, anxious or worried). In addition, participants have the option to add a person not listed, to indicate that they did not seek help from anyone, or to indicate that they/their child did not have a mental health problem in the past 6 months.

The German translation of the Peer Mental Health Stigmatization Scale (PMHSS; McKeague et al., 2015), with a reported internal consistency of Cronbach’s *α* = 0.81, is used to assess stigmatizing attitudes toward children with mental health problems among children, students, parents and teachers. It comprises 11 items rated on a 5-point Likert scale ranging from 1 (strongly agree) to 5 (strongly disagree), for example, “I believe that children with mental health problems are dangerous.” The total stigma score is calculated by summing responses across all items, with reverse coding applied to negatively worded items, whereby a lower score indicates a higher level of stigmatization, and a higher score indicates a lower level of stigmatization.

The stigma of mental disorders among college students is assessed using the validated German version of the Opening Mind Scale for Health Care Professionals (OMS-HC; Modgill et al., 2014; Zuaboni et al., 2021). The German translation of the OMS-HC showed an acceptable internal consistency with Cronbach’s α = 0.74 (Zuaboni et al., 2021). An example item from the scale is as follows, “I am more comfortable helping a person who has a physical illness than I am helping a person who has a mental illness.” The items are then rated by the students on a 5-point Likert scale ranging from 1 (strongly agree) to 5 (strongly disagree).

To screen the mental health status of the children, the KIDSCREEN 10 Index (Ravens-Sieberer et al., 2010; Ravens-Sieberer et al., 2014), both as a self-report completed by the children and as an external proxy report provided by their parents, is used. The instrument consists of 10 items that evaluate the child’s mental health status over the past week, along with one item offering an overall assessment of their health status. It has good internal consistency, with a reported Cronbach’s α of 0.82. An example item is, “Did you feel sad?” Responses are recorded on a 5-point Likert scale ranging from 1 (not at all/never) to 5 (very much/always), with lower scores indicating poorer mental health and higher scores indicating better mental health.

We also assess parents’ mental health using the German version of the Patient Health Questionnaire-4 (PHQ-4; Kroenke et al., 2009; Löwe et al., 2010). The PHQ-4 assesses symptoms of depression and anxiety using four items rated from 0 (not at all) to 3 (almost every day), resulting in a total score of 0–12. Higher scores indicate greater severity of symptoms. The scale has good reliability (Cronbach’s α = 0.85).

Satisfaction with the prevention program is measured among the participating children, teachers and college students who deliver the program, on the basis of Anna Freud’s outcome report (Sharples et al., 2017). Children’s satisfaction with the intervention is measured with an overall evaluation of the lessons: “All in all, I found the project day” 1 (good), 2 (average), and 3 (bad). In detail, children, teachers and college students assess how much they agree with four statements. The project day: (a) “was easy to understand (for the children)”; (b) “was helpful (for the children)”; (c) “was interesting (for the children),” (d) “was fun (for the children),” rated on a 5-point Likert scale ranging from 1 (strongly agree) to 5 (strongly disagree). Children respond using a simplified 3-point Likert scale (1 = agree, 2 = neutral, 3 = strongly disagree). College students and children can indicate whether the lesson was 1 (too short), 2 (too long) or 3 (just right). The children and college students can make comments in 3 open questions about what they liked the most and least, and what else they would have liked from the project day. The teachers are asked four open-ended questions about opportunities, challenges and criticisms of the prevention project, as well as their own experiences and expertise regarding children’s mental health. Teachers are also asked if they can imagine carrying out the project on their own and by whom they would like the project to be carried out by themselves, school social workers, external staff, or others.

The Parental Reflective Functioning Questionnaire (PRFQ; Luyten et al., 2017) is used to assess mentalizing, i.e., a parent’s capacity to understand and interpret both their own and their child’s mental states. The PRFQ consists of 18 self-report items divided into three subscales: Pre-Mentalizing Modes (PM), Certainty about Mental States (CMS), and Interest and Curiosity (IC). An example item is, “I can sometimes misunderstand the reactions of my child.” The items are rated on a 7-point Likert-scale ranging from 1 (strongly disagree) to 7 (strongly agree). Subscale scores are calculated as the mean of the respective items of each subscale. Higher scores on the PM subscale indicate greater difficulties in mentalizing, whereas higher scores on the CMS and IC subscales reflect greater certainty and curiosity about the child’s mental states, respectively. The internal consistency of the scale is acceptable for the PM subscale (Cronbach’s *α* = 0.70), good for the CMS subscale (Cronbach’s *α* = 0.82), and acceptable for the IC subscale (Cronbach’s *α* = 0.75; Luyten et al., 2017).

Parental self-efficacy is assessed using the Parenting self-efficacy questionnaire (FSW; Kliem et al., 2014). Parents rate their parenting self-efficacy using 9 items on a scale ranging from 1 (strongly disagree) to 4 (strongly agree), for example, “I have the ability to set boundaries with my child.” Higher scores indicate higher levels of parental self-efficacy. Good validity and acceptable reliability were found (Cronbach’s α = 0.78–0.79).

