**Methods:**

In this study, the “Talking mental health” (TMH) prevention program is evaluated using a cluster-randomized design, comparing an intervention group with a waitlist control group. The primary outcomes are mental health literacy, stigma and help-seeking behavior. Measurement takes place pre and post, as well as at a six-week follow-up. The sample size aims for 35 school classes with approximately 525 parents and children. The study also examines the effects of an additional parent training on children’s and parents’ mental health.

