This research project investigates whether the school-based prevention program “Talking mental health” (TMH) can increase mental health literacy and help-seeking behavior while reducing the stigma of mental disorders. The primary aim of the prevention project is to improve children’s knowledge and attitudes toward managing difficult emotions. Parents are supported to talk to their children about their feelings and, if necessary, to access appropriate support services. In addition, the effects on college students implementing and being trained in the program are examined.

We expect that children who have completed the TMH program (compared to those in the waitlist control group) will show improved knowledge and skills in managing mental health problems and difficult emotions (increased mental health literacy; Hypothesis 1a), greater willingness to talk about their difficult feelings (increased intentional help-seeking behavior, Hypothesis 1b), increased actual help-seeking behavior (Hypothesis 1c), and reduced stigmatization of mental health problems (Hypothesis 1d). We expect these effects to be present both 1 week after the intervention and at least 6 weeks later. We expect that in the intervention group, an increase in mental health literacy will lead to a decrease in stigma, which in turn will cause an increase in help-seeking behavior (Hypothesis 1e).

Additionally, we expect that parents of children who completed the prevention program (compared with parents in the waitlist control group) will show increased help-seeking behavior for their children (Hypothesis 2a) and reduced stigmatization of mental health problems (Hypothesis 2b).

College students trained in and implementing the TMH program should show less stigmatization toward others than should college students in the control group (Hypothesis 3).

Finally, we expect parents who participate in the parent training program (Emotion focused skills training; EFST-P) and their children to demonstrate improved mental health after the conclusion of the program (Hypothesis 4a). This effect is achieved by increasing parents’ self-efficacy (Hypothesis 4b) and mentalization skills (Hypothesis 4c).

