### Statistical analysis

2.8

Data will be analyzed using the intention-to-treat approach. Multiple imputation will be used to impute missing values. We will analyze and report on attrition. We will check for possible correlations between our variables, primary and secondary outcomes, as well as sociodemographics, and dropout at different time points. Additionally, we will report the reasons given by parents or children for withdrawal. The main analysis is a multilevel analysis due to the nested data structure (children in school classes). Both inter- and intraindividual differences and changes are analyzed. Demographic variables will be included in the data analysis model to control for group differences at baseline. In addition, we will examine a possible mediating effect of increased mental health literacy on increased help-seeking behavior through reduced stigma using multilevel mediation analysis. In addition, we will use correlational analyses as well as chi-squared tests, *t*-tests, Mann–Whitney-U-tests and *F*-tests for group comparisons and comparisons across time points. A significance level of *α* = 0.05 will be used. To validate the newly constructed mental health literacy scale, exploratory factor analysis (EFA) will be conducted, and the comparability of the three vignettes will be checked using ANOVAs. Qualitative data will be analyzed using Mayring’s content analysis using both deductive and inductive approaches (Mayring, 2015). On the one hand, the responses will be matched (deductively) to a pre-established coding scheme to indicate the extent to which the mental health problem is understood by the participating children, and the appropriateness of the help offered by the child. The children’s responses will be grouped blindly by two independent assessors. In the case of discrepancies, the scores will be discussed. On the other hand, categories will be formed (inductively) from the answers to gain more precise insight into the content of the children’s answers.

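### The printed response codes for the children's help-seeking intention score (GHSQ) contradict the stated direction of the summed score; applied as printed, the sign of the Hypothesis 1b effect is reversed

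*Protocol article*

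**What the plan says.** Section 2.6 (Outcome measurements) of the protocol article describes the GHSQ for two groups of respondents.

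- Parents: "Parents respond on a 7-point Likert scale ranging from 1 (extremely unlikely) to 7 (extremely likely".
- Children: "Children respond using a simplified 3-point Likert scale (1 = agree, 2 = neutral, 3 = strongly disagree".
- Scoring, given once with no distinction between the groups: "the sum of the listed eight help sources is used to calculate an overall score for intentional help-seeking behavior".
- Direction, also given once: "Higher scores indicate greater help-seeking intentions".

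No recoding of the children's items is mentioned. For the stigma scale (PMHSS), the same section does state a recode and the resulting direction: "with reverse coding applied to negatively worded items, whereby a lower score indicates a higher level of stigmatization".

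The Abstract says: "The primary outcomes are mental health literacy, stigma and help-seeking behavior". The Introduction makes the children's intention score the subject of a directional hypothesis: "greater willingness to talk about their difficult feelings (increased intentional help-seeking behavior, Hypothesis 1b". Hypothesis 1e, also in the Introduction, ends its mediation chain in help-seeking behavior without saying whether that means intention (GHSQ) or actual behavior (AHSQ).

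**The concern.** The parents' codes rise with willingness to seek help and the children's codes fall with it, yet one sum and one stated direction serve both. The stated direction suits the parents and contradicts the children's codes.

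An error of this kind is hard to see in the output. A reversed score has the same spread, missing-data pattern and two-sided p-value as the correct one. An adverse sign would not look absurd either: the Introduction calls earlier evidence on help-seeking less clear across studies, and the Discussion cites a school programme after which some children's well-being fell. If the printed rule were followed, a helpful programme would be reported as lowering children's intention to seek help, and a harmful one as raising it.

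**Working it through.** The plan gives no figure to reproduce here. The check applies the printed rule to the printed codes.

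**Inputs (all from section 2.6):** k = 8 summed sources; child codes 1, 2, 3 from agreement to strong disagreement; parent codes 1 to 7 from least to most likely; score = sum over the k items; higher is to mean more intention.

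**Step 1. Extremes of the sum as printed.**

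| Respondent | Answer to all 8 sources | Sum | Stated reading |
|---|---|---|---|
| Child | agree | 8 × 1 = 8 | least intention |
| Child | neutral | 8 × 2 = 16 | middle |
| Child | strongly disagree | 8 × 3 = 24 | greatest intention |
| Parent | extremely unlikely | 8 × 1 = 8 | least intention |
| Parent | extremely likely | 8 × 7 = 56 | greatest intention |

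The parents' rows agree with the stated direction. The children's extremes are exactly reversed.

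**Step 2. Effect on the Hypothesis 1b estimate.** Let x be a child's response and S the raw sum. Reversing each item gives 4 − x, so the reversed sum is R = 8 × 4 − S = 32 − S. It runs from 32 − 24 = 8 to 32 − 8 = 24, with high values meaning more intention. For any two groups, mean(R, intervention) − mean(R, control) = −[mean(S, intervention) − mean(S, control)]. R is a linear function of S with slope −1, so in a linear multilevel model the group coefficient changes sign while its standard error and the variance components stay the same. Size, two-sided p-value and two-sided power are therefore unchanged. Section 2.8 says "A significance level of *α* = 0.05 will be used" and does not give sidedness; in a one-sided test p would become 1 − p.

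**Step 3. Hypothesis 1e.** If the GHSQ intention score is the end point, the path into it changes sign, and so does the indirect effect. If the AHSQ is the end point, nothing changes, because it counts sources ticked.

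**Step 4. Which statement is likely to be wrong?** The text points both ways.

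- The child-anchor sentence recurs word for word for the children's satisfaction statements later in section 2.6. Agreement anchors suit those statements but not the GHSQ stem, which asks how likely the child would be to seek help. That suggests a misprint.
- The children's other three-point formats in section 2.6 also give code 1 to the affirmative or favorable answer (vignette items, satisfaction statements, overall rating of the day). That suggests the children's GHSQ may really have been fielded this way round.

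The article does not settle it.

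**The case against.** The strongest reply is that the sentence on direction describes the final score and fixes what is intended, so analysts would recode as a matter of routine. The article never says the items are summed unrecoded, and it is a condensed report. It also leaves out an evidently needed recode elsewhere: the KIDSCREEN-10 sample item about feeling sad is rated from never to always, higher totals are said to mean better mental health, and no reversal is mentioned. The contrast with the PMHSS is therefore weak evidence that no GHSQ recode is planned. The PMHSS statement also concerns negatively worded items within a scale, which is a different matter from the direction of a whole response format. Finally, item-level data allow the sign to be corrected exactly at any time before reporting.

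Most of this stands. A reader might infer that Hypothesis 1b will be concluded in reverse. The documents do not support that, because it needs both an unrecoded sum and a literal reading of the stated direction. Nor do they support saying that Hypothesis 1e is certainly affected, since its end point is not tied to the GHSQ.

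The reply does not remove the contradiction. The article prints the codes, the sum and the direction, and the three do not fit together for the children. Whether the cause is an unstated recode or a misprinted anchor, the printed specification of part of a primary outcome is wrong and needs correcting.

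**Conclusion.** The point holds as an internal contradiction in the scoring of the children's GHSQ. Applied as printed, the most willing child scores 8 and the least willing 24, and the Hypothesis 1b effect is reversed in sign with unchanged size, two-sided p-value and two-sided power. The same applies to Hypothesis 1e only if GHSQ intention is its end point. Parents' GHSQ scores and the AHSQ (Hypothesis 1c) are unaffected.

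The sign reversal is conditional on the printed anchors being those fielded and stored, and on the items being summed without recoding. The documents establish neither. Because the direction of a primary-outcome result depends on the answer, it should be settled before the outcome analysis.

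**What to change.** 1. Confirm the children's GHSQ response labels and stored codes in the fielded questionnaire (tablet and paper versions) and in the survey-tool export.
2. If they are as printed, state that each child item is recoded as 4 minus the response before summing (range 8 to 24, higher = greater intention). If they are not, correct the printed anchors and do not recode. The recode should not be prescribed before step 1: if the stored data already run upward, it would create the reversal it is meant to prevent.
3. As a plausibility check, correlate the final score with the number of AHSQ sources ticked, preferably on t1 data without group labels. The direction of the AHSQ count is unambiguous and the correlation should be positive. Set aside children who report no mental health problem in the period, since their zero count does not mean low help-seeking. A check against the option of seeking help from no one would not serve: if that item shares the same codes, reversing both variables leaves the correlation unchanged, because corr(32 − S, 4 − N) = corr(S, N), where N is the response to that item.
4. Say whether Hypothesis 1e uses the GHSQ or the AHSQ and, if the GHSQ, use the same scored variable.

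The cost is a look at the instrument, at most one scoring line, and a wording change. Section 3.1 reports data already collected in 30 classes; none need be collected again.

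### On its plain reading, the PMHSS scoring rule in section 2.6 contradicts its own response anchors and the stated direction of the stigma total

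*Protocol article*

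**What the plan says.** Section 2.6 (Outcome measurements) gives the response format: "It comprises 11 items rated on a 5-point Likert scale ranging from 1 (strongly agree) to 5 (strongly disagree"). It shows one item: "I believe that children with mental health problems are dangerous". The scoring rule and the direction stand in one sentence: the total is the sum over all items, "with reverse coding applied to negatively worded items, whereby a lower score indicates a higher level of stigmatization", and the sentence adds the converse, that a high total means little stigma.

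The section does not define which items count as negatively worded, list them, or say how many there are. The same scale and rule serve children, parents, college students and teachers.

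The scale matters because, according to the abstract, "The primary outcomes are mental health literacy, stigma and help-seeking behavior". The Introduction expects "reduced stigmatization of mental health problems (Hypothesis 1d") in children. It also expects less stigma in parents (Hypothesis 2b) and in trained college students (Hypothesis 3), and treats stigma as the mediator between literacy and help-seeking (Hypothesis 1e).

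**The concern.** The article states four things together: the anchors, a plainly negative example item, reversal of negatively worded items, and lower total = more stigma. On the ordinary meaning of the words they cannot all hold. With strong agreement coded 1, a hostile statement already gives a low value to a stigmatizing respondent, which is the direction the article wants. Reversing it sends that respondent to the high end.

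What is at stake is the sign of the stigma result. If the data were scored by the plain reading and the total then interpreted as the article states, a program that reduced stigma would be reported as having increased it. This would affect Hypotheses 1d and 2b and the PMHSS part of Hypothesis 3.

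**Working it through.** **Inputs (all from section 2.6).** There are 11 items, scored 1 (strongly agree) to 5 (strongly disagree). A reversed response is 6 − x. The number of stigmatizing items, s, is not given, so it is varied from 0 to 11; the other 11 − s items are favourable statements.

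**Extreme respondents.** The most stigmatizing respondent answers 1 to every stigmatizing item and 5 to every favourable one. The least stigmatizing respondent answers 5 and 1.

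**Step 1: what reproduces the stated direction.** Reverse the favourable items only.
- Most stigmatizing: s × 1 + (11 − s) × (6 − 5) = 11
- Least stigmatizing: s × 5 + (11 − s) × (6 − 1) = 55

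Lower means more stigma, as stated, for every s.

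**Step 2: the plain reading.** Reverse the stigmatizing items only. For the example item, strong agreement becomes 6 − 1 = 5. For the total:
- Most stigmatizing: s × (6 − 1) + (11 − s) × 5 = 55
- Least stigmatizing: s × (6 − 5) + (11 − s) × 1 = 11

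Higher means more stigma, the opposite of the statement, again for every s.

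**Step 3: the anchors as the possible error.** Suppose the questionnaire in fact used 1 = strongly disagree and 5 = strongly agree, and the stigmatizing items are reversed.
- Most stigmatizing: s × (6 − 5) + (11 − s) × 1 = 11
- Least stigmatizing: s × (6 − 1) + (11 − s) × 5 = 55

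The stated direction is recovered.

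**Step 4: no reversal, for comparison.** Under the stated anchors the most stigmatizing respondent totals 55 − 4s and the least 11 + 4s. With s = 5 this is 35 against 31; with s = 6 it is 31 against 35. If the scale mixes both kinds of item, some reversal is needed, so dropping the rule is no remedy.

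| Key | Most stigmatizing | Least stigmatizing | Matches the stated direction? |
|---|---|---|---|
| Favourable items reversed, anchors as stated | 11 | 55 | Yes |
| Stigmatizing items reversed, anchors as stated | 55 | 11 | No |
| Stigmatizing items reversed, anchors exchanged | 11 | 55 | Yes |

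**Step 5: what changes in the analysis.** Under the stated anchors, the keys in steps 1 and 2 differ by 6 − x on every item, so one total is 11 × 6 = 66 minus the other (66 − 11 = 55). A between-arm difference D becomes −D. The standard deviation, the absolute effect and the two-sided p-value stay the same. In Hypothesis 1e the literacy-to-stigma path a and the stigma-to-help-seeking path b both change sign, and (−a)(−b) = ab, so the indirect effect is unchanged.

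**Step 6: which check can detect it.** Correlations between items are identical under the two keys, because the covariance of 6 − x and 6 − y equals that of x and y. Positive inter-item correlations therefore cannot reveal a complete reversal. Comparing the answer to the example item, before recoding, with the total can.

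**The case against.** The best defence is that negatively worded may be meant technically, as keyed against the construct. On a scale of stigmatization those are the favourable statements, and reversing them gives exactly the stated direction (step 1). The example item illustrates the response scale and is never named as reversed; left alone, it already runs as the article wants. The direction is spelled out both ways, so the intention is not in doubt, and an analyst would have to overlook it to report the wrong sign. One could add that item keys usually sit in fuller documents.

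Part of this stands. A reader might infer that the stigma result is bound to come out reversed, or that the reversal rule is certainly the faulty element. The article supports neither: the technical reading is possible, and the anchors could be what is misreported. Nor does it suggest that different groups would be scored with different keys, since one rule is given for all. College students also complete a second stigma scale, the OMS-HC, so Hypothesis 3 does not rest on the PMHSS alone.

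The rest does not stand. The technical reading requires calling accepting statements negative and a statement that children are dangerous not negative, and nothing in the text signals that usage. This is also not a detail left to another document: the article chose to state a scoring rule, and the rule conflicts with the text around it. Section 2.6 gives little ground for assuming that directions were checked. Children's help-seeking intentions are answered from 1 = agree to 3 = strongly disagree and summed, with higher said to mean greater intention and no reversal mentioned.

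**Conclusion.** The scoring rule is wrong as written on its plain reading, and should be fixed before the stigma data are analysed. Under that reading the extremes are 55 and 11 where the stated direction needs 11 and 55, whatever the mix of items. The consequence would be a reversed sign and interpretation for Hypotheses 1d and 2b and the PMHSS part of 3, with magnitude, two-sided p-values and the 1e indirect effect untouched.

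This rests on two assumptions: that negatively worded items are statements like the example, and that the anchors are reported correctly. If either fails in the way described above, the data may be scored correctly and only the text needs repair. Scoring is done after collection, so nothing is lost.

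**What to change.** 1. Confirm from the questionnaire as presented to respondents which anchors were used.
2. If 1 = strongly agree is right, replace the rule in section 2.6 with: items expressing stigma are kept as scored, items expressing acceptance are reversed (6 minus response), and higher totals mean less stigma. If the anchors turn out to be the other way round, correct the anchors and say that the items expressing stigma are the ones reversed.
3. List the reversed item numbers and apply the one key to children, parents, college students and teachers.
4. Before arm is attached, check that respondents who agree with the item about children being dangerous, using the answer before recoding, have lower totals. Do not rely on inter-item correlations for this.

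The cost is one sentence, a scoring key and one tabulation. Section 3.1 reports data from 30 classes with 6 more planned; the change affects neither the data already held nor further collection.
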